### Sample Size

At least 42 patients with breast cancer will be recruited for the study. The patients will be divided into 3 experimental groups, each consisting of 14 patients, based on the type of treatment performed (tDCS only, exercise therapy only, or combined treatment). In case of dropouts, the recruitment of patients will continue until 42 participants complete the treatment.

Since the present study is the first to evaluate the effects of tDCS in patients with different types of chronic pain over a 3-week period, to estimate the expected difference between the effect of tDCS and combined therapy (tDCS and exercise therapy), for the calculation of the sample size we relied on a recently published study [54] of 45 patients with fibromyalgia to calculate the sample size. The published study compared the effects of tDCS and exercise therapy if carried out individually or in combination for 1 week. The improvements observed in the 3 treatment groups are shown in the Table 4.

**Table 4 table4:** Mean visual analogue scale (VAS) scores of the different treatment groups.

Treatment group	Baseline VAS	Improvement (%)	VAS at 1 week after treatment	ΔVAS (beginning of treatment vs 1 week after treatment)
tDCS^a^	7.2	18	5.904	1.296
Combined therapy	7.3	40	4.4019	2.8981
Exercise therapy	6.8	24	5.202	1.598

^a^tDCS: transcranial direct current stimulation.

The sample number for each individual clinical center was calculated to demonstrate the difference between the change in the visual analogue scale (VAS) value at the beginning of treatment and after 1 week of treatment between the group of patients receiving tDCS and that receiving combined therapy. A Wilcoxon-Mann-Whitney test was performed using G*Power V3 software [57] with an effect size of 1 and assuming the following parameters: a VAS change of 1.3 in the tDCS treatment group and 2.9 in the combined therapy group, as reported by Mendonca et al [54] in the evaluation after 1 week of treatment; an SD of 1.27 in both groups; a type 1 error of 0.05; and a power of 80%. A sample of the same size is adequate to demonstrate the difference in VAS between the exercise therapy group and the combined therapy group (based on data from Mendonca et al [54]).

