### Statistical Analysis

To evaluate the efficacy of the treatments, a statistical analysis will be conducted on the clinical scales, functional tests, and questionnaires using a dedicated software. Data distribution will be evaluated using Shapiro-Wilk tests. In the case of a normal distribution, statistical significance will be evaluated by applying parametric *t* tests and ANOVA for repeated measures. In case the assumption of a normal distribution is not supported, a nonparametric Wilcoxon-Mann-Whitney test will be used. Statistical analysis will be performed on all participants who complete the treatment required by the protocol. Participants who do not complete all phases of the study (ie, dropouts) will be excluded from the data analysis. Furthermore, as suggested by recent scientific literature, Bayesian statistics will also be applied using JASP open-source software in order to better estimate the possible absence of an effect of therapeutic strategy [58]. In particular, intragroup comparison analysis will be assessed using repeated measures ANOVAs (within subjects, time factors). Comparison of the subgroups (n=14 per group) will be performed using parametric or nonparametric hypothesis tests depending on the normality of the data distribution and corrections of type 1 errors. Finally, correlations will be performed between the VAS, patient demographics, and clinical data. All secondary outcomes will be evaluated by descriptive statistical analysis. Analysis will be carried out using SPSS Statistics (version 27; IBM).

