### Study Limitations

A main limitation of the present study could be the personal use of the home care strategy. Despite the many advantages of this technological approach, some patients may find it difficult to use the equipment without direct assistance from a health care professional. The self-management of the home care strategy could also have a negative influence on treatment adherence, causing possible dropouts during the study phases. For these reasons, it will be necessary to monitor patients’ motivation during treatment to prevent patients from neglecting rehabilitation.

Patients should also be adequately informed of the possible risks linked to the administration of the treatments to reduce concerns about the occurrence of possible adverse effects of tDCS. In particular, adverse events could involve the appearance of local effects of the stimulation consisting of a slight burning sensation or skin redness. Nevertheless, it should be noted that participation in a trial involves strict control by the experimenter to limit any problems that may arise.

Furthermore, the initial recruitment via social media and email could orient the sample toward younger and technologically experienced patients. However, we adopted this instrument to promote the recruitment of patients throughout the country to overcome geographical barriers related to the access to health care. Additionally, due to the use of digital devices during the rehabilitation program proposed in this study protocol, the enrollment of technologically savvy patients with breast cancer could facilitate the use of the home-based treatment.

Finally, given the importance of subjective perception on the classification of pain, we chose to adopt several self-report tools to assess the personal experience of the patients with breast cancer. However, these instruments have limitations, as it is not possible to obtain objective information. When drawing conclusions, it will therefore be necessary to consider that the data may be influenced by various personal factors.

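### Dropouts are excluded and replaced, so the efficacy comparison is between completers and is open to bias of unknown direction if dropout is outcome-related and uneven across arms

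*Protocol article*

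**What the plan says.** Three statements in the protocol article fix who is analysed.

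- Statistical Analysis, on who is included: "Statistical analysis will be performed on all participants who complete the treatment required by the protocol".
- Statistical Analysis, next sentence, on who is left out: "Participants who do not complete all phases of the study (ie, dropouts) will be excluded from the data analysis".
- Sample Size, on replacement: "In case of dropouts, the recruitment of patients will continue until 42 participants complete the treatment".

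The group comparison is then described with 14 per group: "Comparison of the subgroups (n=14 per group) will be performed using parametric or nonparametric hypothesis tests". No analysis of all randomised patients, and no sensitivity analysis for dropout, appears in the article.

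The Study Limitations section recognises the risk: "The self-management of the home care strategy could also have a negative influence on treatment adherence, causing possible dropouts during the study phases". Table 2 (Randomization) shows unequal burden. Groups A and B each receive one therapy; group C has tDCS three days a week with exercise on the days between. According to the Intervention section, assessments run from baseline through 1 week, 3 weeks and 1 month to 3 months.

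**The concern.** The trial's main question is whether the combination beats either treatment alone. Randomisation supports that comparison only for the patients as randomised. Once patients who leave are removed and others take their place, each arm holds those able and willing to finish that arm's programme. If the reasons for leaving are linked to pain response and operate differently in the three arms, the completers differ for reasons other than treatment. Replacement restores the head count, and so the nominal power, but not comparability.

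A second problem lies in the wording. One sentence turns on finishing the treatment (3 weeks), the other on finishing all phases of the study. If follow-up counts as a phase, a patient with VAS observed at 1 and 3 weeks who misses the 3-month questionnaire is excluded, yet she is not replaced because she completed treatment. The trial was sized on the 1-week change, so fully observed data on that endpoint could be discarded.

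**Working it through.** **The plan's own number.** Inputs from Sample Size: Wilcoxon-Mann-Whitney test, effect size 1, type 1 error 0.05, power 80%. Using the noncentral t with efficiency 3/π, 14 per group gives power 0.81 one-sided (0.70 two-sided). The stated 14 per group is reproduced on the one-sided reading; the article does not state sidedness.

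**How many randomised patients would be left out.** The article gives no dropout rate, so 10%, 20% and 30% are assumptions. Number randomised to reach 42 completers = 42/(1 − rate):

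- 10%: 42/0.90 = 46.7, so 47 randomised and 5 left out.
- 20%: 42/0.80 = 52.5, so 53 randomised and 11 left out.
- 30%: 42/0.70 = 60 randomised and 18 left out.

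**Size of the bias with no true effect.** SD 1.27 is from Sample Size. Let z be the standardised VAS improvement. Assume P(dropout | z) = 1/(1 + exp(−(a − b·z))), with b = 1 or 2 (log-odds per SD) and a chosen to give overall dropout q. The completers' mean is shifted by 1.27 × E[z(1 − P)]/(1 − q), and the bias is the difference in shift between arms. Type I error is from simulation with 14 completers per arm and a two-sided t test at 0.05.

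| Dropout, arm 1 vs arm 2 | Bias, VAS points (b = 1 to 2) | Type I error |
|---|---|---|
| 20% vs 20% | about 0 | about 5% |
| 20% vs 10% | 0.10 to 0.15 | about 5 to 6.5% |
| 30% vs 10% | 0.20 to 0.29 | 7 to 10% |
| 30% vs 0% (extreme) | 0.32 to 0.48 | 10 to 18% |

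The bias favours the arm with more dropout. As an analytic bound, if the worst-responding 20% of one arm all leave and nobody leaves the other, the shift is 1.27 × φ(z at 0.20)/0.80 = 1.27 × 0.280/0.80 = 0.44 points. The planned difference between tDCS and combined therapy is 2.9 − 1.3 = 1.6 points.

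**Direction when the planned effect is real.** Apply one response-driven dropout rule to both arms, with 20% dropout in the single-treatment arm and a true difference of 1.6.

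- b = 1: single arm shifted up 0.22, combined arm 0.09; completers' difference 1.6 + 0.09 − 0.22 = 1.47.
- b = 2: shifts 0.33 and 0.08; completers' difference 1.6 + 0.08 − 0.33 = 1.35.

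Here the bias goes against the combined arm.

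**If missed follow-up also excludes.** On the one-sided reading above, power is 0.81 with 14 per group, 0.75 with 12 and 0.67 with 10.

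**The case against.** The strongest reply concerns direction and size. A reader might infer that the plan will favour the combined arm, because it is the most demanding and those who do not benefit leave. The document does not support that. It requires excess dropout in the combined arm that is also selective on response, which no section states. If non-response drives dropout, the less effective arms lose more patients and a true advantage shrinks. The Study Limitations section attributes dropout to self-managing the treatment at home, which applies to all three arms, so a large imbalance is not a given. With a modest imbalance the type I error barely moves. These points stand, and they limit the claim to openness to bias.

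The second reply is that the two exclusion sentences need not conflict. The second glosses the excluded patients as dropouts, and Sample Size contrasts dropouts with patients who complete treatment. Read that way, finishing treatment is the only criterion, and 14 per group is preserved. This is a fair reading; the wording is ambiguous, not a proven contradiction.

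Third, a reader might infer that usability results are certain to be inflated. Patients who could not manage the system may well be missing from them, but SUS and MARS are asked at the end of treatment, so scores from those who have left may simply not exist.

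The reply that an unseen analysis plan may deal with this does not stand. The exclusion is an explicit rule here, and an analysis plan that kept all randomised patients would contradict it.

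**Conclusion.** The point holds: the article prescribes a completers' comparison with replacement for the trial's main question and sets no all-randomised analysis beside it. The rule itself is certain. Its effect is conditional on dropout being related to VAS response and differing between arms; both are plausible, neither is established. Under the assumed rates the spurious difference runs from about zero (equal dropout) to just under half a VAS point (30% versus 0%). Moderate imbalances give 0.10 to 0.29 points and type I error up to about 10%. The direction is unknown. The plan also discards the outcome data that would help to judge whether the conditions for bias are met. Separately, the differing completion criteria leave it unclear whether the planned 14 per group is secure.

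**What to change.** Replace both exclusion sentences in Statistical Analysis with text to this effect:

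> The primary analysis includes all randomised patients in the arm to which they were allocated and uses every available VAS assessment, for example in a likelihood-based repeated-measures model. Patients who stop treatment continue to receive the questionnaire links. Dropouts remain in the analysis alongside any additional patients recruited. An analysis of treatment completers, meaning patients who finish the 3-week treatment, is a sensitivity analysis.

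The Sample Size rule of recruiting to 42 treatment completers can stay, provided the added patients supplement the dropouts. Report the number of dropouts by arm next to the SUS and MARS results.

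The cost is a small procedural change, possibly a protocol amendment, since questionnaires must continue after treatment stops; they already go out by web link. The estimated effect may be smaller. A model that assumes data are missing at random does not remove bias where VAS is missing because of its own unobserved value. Continued follow-up is therefore the more important part, and the particular model is secondary with groups this small.

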**Objective:**

We aimed to investigate the effectiveness of a home care strategy combining computerized rehabilitation, transcranial direct current stimulation (tDCS), and remote telemonitoring via a web-based platform in patients with breast cancer suffering for chronic pain.

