**Methods:**

A web-based structured survey aimed at monitoring chronic pain and its effect on psychological functions will be delivered to patients with breast cancer through social media and email. In total, 42 patients with breast cancer affected by chronic pain will be recruited during the medical screening visit. The patients will be randomly divided into 3 treatment groups that will carry out either tDCS only, exercise therapy only, or a combination of both over a 3-week period. All the treatments will be delivered at the patients’ home through the use of a system including a tablet, wearable inertial sensors, and a tDCS programmable medical device. Using web-based questionnaires, the perception of pain (based on the pain self-efficacy questionnaire, visual analogue scale, pain catastrophizing scale, and brief pain inventory) and psychological variables (based on the hospital and anxiety depression scale and 12-item short form survey) will be assessed at the beginning of treatment, 1 week after the start of treatment, at the end of treatment, 1 month after the start of treatment, and 3 months after the start of treatment. The system’s usability (based on the mobile app rating scale and system usability scale) and its involvement in the decision-making process (based on the 9-item shared decision-making questionnaire) will be also evaluated. Finally, at the end of the treatment, a digital focus group will be conducted with the 42 patients to explore their unexpressed needs and preferences concerning treatment.

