**Conclusions:**

We expect that the combination of tDCS and telemedicine programs will reduce pain perceived by patients with breast cancer and improve their mental well-being more effectively than single interventions. Furthermore, we assume that this home-based approach will also improve patients’ participation in routine clinical care, reducing disparities in accessing health care processes. This integrated home care strategy could be useful for patients with breast cancer who cannot find relief from chronic pain with pharmacological treatments or for those who have limited access to care due to poor mobility or geographical barriers, thus increasing the patients’ empowerment and reducing health care costs.

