### Conclusion

The Technopain protocol is a new home care strategy that combines computerized training rehabilitation, noninvasive neuromodulation, and remote telemonitoring via a web platform for the treatment of psychosocial and physical symptoms related to chronic pain in patients with breast cancer. In particular, this approach will evaluate the impact of chronic pain on patients’ quality of life and will offer a rehabilitation program that can favor the treatment of the greatest number of patients through home delivery. This trial will primarily evaluate the fluctuation of perceived pain by patients during and after treatments, evaluating which of the different types of treatments is the most effective between the single treatments or their combination. In particular, we expect that this study will provide a useful treatment for all patients who cannot find relief from chronic pain with pharmacological treatments. Our ultimate aim is to encourage the development of personalized telemedicine, which can provide daily clinical assistance to patients, eliminating the economic and geographical barriers related to the use of health services.

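### With three active, home-delivered arms and no control, the trial estimates only relative effects, but the objective and the within-arm and Bayesian analyses are worded as tests of absolute efficacy

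*Protocol article*

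**What the plan says.** **Arms.** Patients are "randomly divided into 3 treatment groups that will carry out either tDCS only, exercise therapy only, or a combination of both" (abstract, Methods; detailed in Table 2 under Randomization). The abstract also has every treatment given at home. No sham, untreated, usual-care or clinic arm is described.

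**Objective.** The abstract states: "We aimed to investigate the effectiveness of a home care strategy combining computerized rehabilitation", with tDCS and remote telemonitoring. The Aims section likewise speaks of evaluating the new home care strategy as a whole.

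**Comparative question.** A narrower question also appears. The abstract Conclusions expect the combination to do better than single interventions. The closing Conclusion section asks which of the single treatments or their combination works best. The Sample Size section is built on combined versus tDCS and says the same size serves for combined versus exercise.

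**Analysis.** The Statistical Analysis section opens by announcing an evaluation of treatment efficacy. It plans between-group tests with 14 per group and Bayesian statistics "in order to better estimate the possible absence of an effect of therapeutic strategy". The sentence after that, introduced as a specification, plans intragroup repeated-measures ANOVAs with time as the factor.

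**Interpretation.** The closing Conclusion section says "we expect that this study will provide a useful treatment for all patients who cannot find relief from chronic pain with pharmacological treatments". The abstract Conclusions assume that the approach will improve "participation in routine clinical care, reducing disparities in accessing health care processes". Study Limitations concedes of the self-report tools that "these instruments have limitations, as it is not possible to obtain objective information". It mentions neither the absence of a control nor patients' awareness of their treatment.

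**The concern.** The objective and part of the analysis ask whether the strategy works. The randomisation can say only whether one active home treatment works better than another.

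Two unsupported conclusions become possible if the text is followed as written. First, pain may fall over time in all three arms and the intragroup ANOVAs may be significant. Under an efficacy heading, that would read as proof of benefit. Second, the Bayesian analysis may favour the null and be reported as absence of an effect of the strategy. If the contrast was between arms, it would show only that active arms are similar. If it was change over time, it would have no comparator at all.

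**Working it through.** **1. What the randomised contrasts identify**

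| Question | Contrast needed | In the design? |
|---|---|---|
| Does adding exercise to tDCS help? | C vs A | Yes |
| Does adding tDCS to exercise help? | C vs B | Yes |
| Is tDCS better than exercise? | A vs B | Yes |
| Does the strategy work in absolute terms? | Any arm vs sham, usual care or no treatment | No |
| Does home delivery or telemonitoring matter? | Home vs clinic, or with vs without telemonitoring | No |

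**2. The plan's own figure.** Inputs from the Sample Size section: effect size 1, type 1 error 0.05, power 80%, Wilcoxon-Mann-Whitney test. The asymptotic relative efficiency method with a normal parent uses an effective n of 14 × 3/π. One-sided, this gives 14 per group (power 0.808), which reproduces the plan. Two-sided, power at 14 per group is 0.70. The calculation concerns combined versus single treatment only; nothing in it addresses an absolute effect.

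**3. Regression to the mean in within-arm change.** Textbox 1 requires VAS >4. The other inputs are my assumptions: VAS in the source population is normal with mean μ and SD 2 (scale limits ignored), and test-retest correlation r is 0.5 to 0.7. The screening value is treated as the baseline.

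Formulas: E[X | X>4] = μ + 2·φ(a)/(1−Φ(a)), with a = (4−μ)/2. Expected fall without any treatment effect = (1−r)·(E−μ).

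Scenario 1, with the source mean assumed:
- μ = 3: a = 0.5, E = 3 + 2×0.352/0.309 = 5.28. Fall = 0.5×2.28 = 1.14 (r = 0.5) or 0.3×2.28 = 0.68 (r = 0.7).
- μ = 4.5: a = −0.25, E = 4.5 + 2×0.387/0.599 = 5.79. Fall = 0.5×1.29 = 0.65 or 0.3×1.29 = 0.39.

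Scenario 2, with μ solved so that the enrolled mean equals a Table 4 baseline:
- Enrolled mean 7.2 (tDCS row): μ = 6.90, excess 0.30. Fall = 0.15 or 0.09. Against the tabulated change of 1.296, that is 12% or 7%.
- Enrolled mean 6.8 (exercise row): μ = 6.34, excess 0.46. Fall = 0.23 or 0.14. Against 1.598, that is 14% or 9%.

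**4. How much a between-arm null could show.** With 14 versus 14 and the plan's SD of 1.27, the 95% confidence interval half-width for a difference in VAS change is t(0.975, 26)·SD·√(2/14) = 2.056×1.27×0.378 = 0.99 points. For a default two-sample Bayesian t test with a Cauchy prior of scale 0.707 (assumed, since the article gives no prior), the Bayes factor for the null is largest at t = 0, where it is 2.8. Even identical arm means would support equality only weakly.

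**The case against.** The strongest reply is that the comparative question is already in the article. The abstract Conclusions and the closing Conclusion section ask whether the combination beats the single treatments, and the sample size is set for that. A design that compares a combination with its components is a legitimate way to learn whether combining adds benefit. This stands: a reader might infer that the randomised comparison cannot address effectiveness at all, and that goes too far.

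Four other stronger readings are tempting.

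- *Access and cost are untestable aims.* The Aims section names neither. They appear as expectations or hypotheses in the abstract Conclusions and the Discussion, and the Statistical Analysis section does not analyse them. Table 1 has no measure of either, so the trial does not test them, but they are not failed objectives.
- *The plan will declare the strategy ineffective if the arms are equal.* No such decision rule is written. The Bayesian sentence can be read as a null between arms, which is estimable. The defect is that the contrast is not named.
- *Regression to the mean explains most of the assumed tDCS change.* Dividing scenario 1 by 1.296 gives 0.39/1.296 = 30% to 1.14/1.296 = 88%. That scenario implies an enrolled mean of 5.3 to 5.8, while the tDCS row in Table 4 starts at 7.2; matching 7.2 gives 7% to 12%. The fall would be smaller still if the assessment before treatment is separate from the screening visit. It is also expected equally in all arms, so it does not bias the between-arm contrasts.
- *The trial is open-label.* The article does not mention blinding. Without a sham, a patient could hardly be unaware of receiving tDCS, exercise or both, but this is an inference.

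**Conclusion.** The point holds in a limited form. The design identifies relative effects among tDCS, exercise and their combination, and nothing more. The objective and the efficacy wording around the intragroup ANOVAs and the Bayesian null reach further, and Study Limitations does not warn of this.

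Regression to the mean could contribute about 0.1 to 0.2 VAS points to within-arm change if patients resemble Table 4, and 0.4 to 1.1 points if they come from a source with mean 3 to 4.5. Both ranges rest on the assumed SD of 2, correlation of 0.5 to 0.7 and screening value used as baseline. Natural course and placebo response come on top and cannot be sized from the article. The main conclusion does not depend on these figures, because an uncontrolled change over time cannot establish efficacy whatever the size of each part.

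This should be corrected. It does not undermine the combined-versus-single comparison.

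**What to change.** 1. Abstract, Objective: restate it as the relative effect of combined home treatment versus each single treatment, and of tDCS versus exercise.
2. Statistical Analysis: base efficacy inference on between-arm contrasts of VAS change. Label the intragroup ANOVAs as descriptive and not as evidence of efficacy.
3. Statistical Analysis: limit the Bayesian null to no difference between combined and single treatment, and state that it cannot show the strategy to be ineffective.
4. Study Limitations: add the missing control and patients' likely awareness of their treatment. Keep the access and cost statements as hypotheses that the trial does not test.

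I would not add a rating of expected benefit, taken once the arm is known, as an adjustment variable. It is measured after randomisation and can be affected by assignment, so conditioning on it with 14 per arm may introduce bias and would not isolate an expectation-free effect.

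The cost is wording only, with no new arm, patients or measurements. The downside is that the claims become narrower.
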